**Figure 2 F2:**
[figure not shown]
Data flow: a description of how the data flows from new variables being input into the EuroKing maternity system to analysis. NHS, National Health Service; NNRD, National Neonatal Research Database.

### Opportunity to Opt-Out

This study will use data collected in NHS electronic systems that will be pseudonymised prior to transfer to the CU study team (table 1). Approval for the transfer of identifiable patient data from WS to NNRD in order to match the infants transferred to NNU has been obtained under Section 251 (s251) of the NHS Act 2006.

Participants will have the option to opt-out by informing the maternity unit that they do not wish to participate. CU will provide individual sites with patient information leaflets, posters and take-home cards. Individual sites are responsible for ensuring all women are provided with relevant information to ensure they are aware of the option to opt-out.

### Qualitative component

The aim of the qualitative component of the study is to identify and explore factors which influence the use of birth pools and giving birth in water.

Phase 1:

Six closed online discussion groups hosted on the CU website and telephone interviews:

Women with recent experience of maternity services.Heads of midwifery and midwifery managers.Consultant midwives.Band 5/6 clinically focused midwives.Obstetricians.Neonatologists and paediatricians.

Phase 2:

In-depth organisational case studies across three study sites, comprising midwifery-led and obstetric units with a range of waterbirth rates. Data points:

Key documents, online information and existing data relating to pool use and waterbirth.Information relating to unit equipment and facilities.Group or individual discussions with staff and lay representatives.

### Study participants inclusion and exclusion criteria

Cohort study:

Main analysis: All women at low-risk of complications who use a birth-pool or bath for water immersion during established labour between 1 January 2015 and the end of data collection. Women will be classified as ‘low risk’ if they are at term (37+^0^–41+^6^ weeks gestation), with a singleton assumed cephalic fetus, in spontaneous labour and without pregnancy or intrapartum factors identified by NICE that indicate a need for obstetric or other medical care in labour.

Women who freebirth or give birth prior to arrival at their chosen place of birth or prior to the arrival of a midwife will be excluded.

Descriptive analysis: All women giving birth at a participating NHS site between 2015 and study end.

Eligible sites: NHS maternity services using EuroKing with waterbirth facilities.

Qualitative component phase 1:

(Participants must be from the UK, either within or outside study sites).

Online discussion group participants:

Pregnant women or who have given birth within the last 12 months.Midwives (all grades/positions).Neonatologists, obstetricians and paediatricians (including trainees).

Telephone interview participants:

UK Neonatologists*.Obstetricians*.Paediatricians*.*(including trainees)

Qualitative component phase 2:

Purposively selected case study sites to include midwifery and obstetric units with a range of waterbirth rates (excluding units without a waterbirth facilities).

In each case study site, participants are purposively sampled for discussions, to include the following:

Midwives representing a range of grades and positions.Obstetricians, neonatologists and paediatricians (including trainees).Other unit staff as identified.Women who have given birth in the unit recently.Lay representatives who have experience of supporting local women who have given birth recently—for example, doulas.

### Recruitment/opt-out

For the cohort study, data will be collected on all women and babies born at participating sites from 1 January 2015 until study end date unless they choose to opt-out of the study.

The online discussion groups will be advertised via social media, magazine articles, email circulation and leaflets/flyers handed out at conferences. Adverts will provide a brief overview of the discussion groups and a website link which will contain study overview, a participant information sheet (PIS) and discussion group ground rules. If keen to participate, individuals will submit their email address via the website, which will generate an automated email invitation with a link to the discussion group registration page. Participants will be asked to complete an online consent form, create an anonymous public forum name and password to log in to the discussion, and click to confirm that they agree to comply with the discussion group ground rules.

The telephone interviews will be advertised via professional and lay networks, including social media and email circulation. Adverts will provide a brief overview of the study and the purpose of the interviews, together with a contact email address for those interested in taking part. Potential participants will be emailed a copy of the PIS and given the opportunity to ask questions. Those who would like to take part will be asked via email to agree a date for the interview.

For phase 2 of the qualitative work, data provided by sites will be used to identify midwifery-led and obstetric units, enabling the team to work with sites with both low and high waterbirth rates. Once potential sites are identified, the site Principal Investigator (PI) will be contacted by a member of the study team, provided with information about the case studies and invited to take part. For the discussions within the case study sites, the study will be publicised at unit meetings and via local networks, and potential participants requested to contact the research team to receive information. Researchers will also approach staff members and lay representatives directly to encourage voluntary participation. A PIS and opportunity to ask questions will be provided. Those who would like to take part will be asked to contact the researchers to arrange to participate in a discussion.

#### Justification of approach

The POOL Study will collect data on 600 000 mother/infant dyads with three years of these data having been collected in electronic systems prior to site opening. It is not practical to ask for consent from every woman and doing so would inevitably lead to an incomplete cohort and potentially a biased sample. The study will involve the transfer of personal data to NNRD and for this we are using an opt-out model under s251, as approved by the Confidentiality Advisory Group (CAG).

#### Development of the opt-out leaflet/cards

We worked closely with the study patient and public involvement (PPI) representatives on the wording of these documents. A key consideration was to ensure that there were multiple time points for the mother to opt-out of the study throughout her episode of maternity care, by informing a midwife or making contact with the maternity unit. In addition to informing all women during pregnancy that the study is running in their maternity unit, any woman who uses a pool during labour or birth will be provided with a take-home card. This will reinforce the option to opt-out of the study with relevant contact details. The final text was approved by both an NHS Research Ethics Committee (REC) and CAG committee as part of the overall governance approval for the study.

#### Process to manage opt-out

If opt-out is selected, a healthcare worker will select the opt-out option on EuroKing, automatically generating a filter so that WS will not extract the mother’s/infant’s data, nor will data be sent to the NNRD. It was not practical to offer the chance to opt-out to women who gave birth at participating units in the period between 1 January 2015 and date of site opening.

For the online discussion groups, participants may contribute as much or as little as they wish. For face-to-face and telephone discussions, participants have the right to decline or withdraw consent at any time, without any effect on their care or employment.

### Patient and public involvement

Lay persons were involved in the original grant proposal, development of research questions, study design and outcomes. The study management group and the study steering committee have PPI representatives who were actively engaged in study design and study conduct.

### Governance and compliance

Following REC approval (18/WA/0291) and s251 support (18CAG0153) retrospective data extracts were made from the pilot site. New variables were added to EuroKing for the commencement of prospective data collection.

In order to satisfy the requirements of the s251 support the Data Security and Protection Toolkit (DSPT)^9^ commissioned by the Department of Health for NHS Digital to develop and maintain) was required for both WS (registered as Healthcare Software Solutions) and NNRD (registered as Chelsea and Westminster Hospital NHS Foundation Trust). This organisation-level assessment provides reassurance of satisfactory information governance within the two organisations. Both the s251 support and DSPT are assessed and renewed on an annual basis.

### Analysis

#### Sample size

The non-inferiority of birth in water compared with birth on land on rates of OASIS will be examined by parity. The Birthplace in England study found that overall 4.6% and 1.6% of nulliparous and parous women respectively, sustained OASIS.^10^ A sample size of 15 000 nulliparous and 15 000 parous low-risk women (7500 each water and land) is required to obtain 90% power, and a 95% one-sided CI around a treatment difference of zero. A non-inferiority margin of 1% or less, and 0.6% or less will be taken as clinically non-significant among nulliparous and parous low-risk women, respectively. Since nulliparous women birthing in water are regarded as the least prevalent of the four groups, the data collected would provide data on 7500 would ensure adequate numbers in the other three, more prevalent groups. These data will be combined to assess the effects averaged across both strata at an increased power, with a sample size of 30 000 low-risk women. We have assumed that 25% of the 6600 waterbirths recorded in EuroKing in 2015 were nulliparous women (1650/annum). For the infant primary outcome, an estimate of 5% is used for the proportion of infants born to low-risk mothers experiencing ‘adverse infant outcome or treatment’.^11^ A non-inferiority margin of 1.0% or less will be taken as clinically non-significant. A sample size of 16 200 infants (8100 per group water/land) are required to have 90% power, and a 95% one-sided CI around a treatment difference of zero.

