### Main analysis

Primary analysis will compare maternal and infant outcomes only between women without identified pregnancy or intrapartum complications ‘low risk’ who stay and give birth in the pool (waterbirth, group 1) compared with women without identified pregnancy or intrapartum complications ‘low risk’ who use water immersion during their labour but decide to leave the water for birth (out of water, group 2).

The primary analyses are based on a non-inferiority test of birth in water vs on land, comparing (1) the proportion of mothers that have OASIS (based on retrospective and prospective EuroKing data) and (2) the proportion of infants with a composite outcome of ‘adverse infant outcome or treatment’ (based on prospective EuroKing and NNRD data).

To test the primary hypothesis of non-inferiority between birth in water and on land, the maternal and infant primary outcomes will be evaluated for non-inferiority using logistic regression models, in the first instance with no adjustment for covariates. Adjusting for potential confounders may result in a more precise treatment effect estimate. The potential confounders of both primary outcomes (listed in table 2) will be considered. Directed acyclic graphs; visual representations of causal assumptions will be used to identify the presence of confounders.

**Table 2 T2:** Potential confounders for both maternal and infant primary outcomes

	**Maternal outcome: OASIS**	**Adverse infant composite outcome**
Maternal age (years)	X	X
Maternal BMI	X	X
Parity	X	
Duration of labour	X	X
Gestational age at delivery (weeks)	X	X
Birth weight (g)	X	X
Infant head circumference (cms)	X	
Maternal thyroid disease (including hypothyroidism)		X
Prelabour ruptured membranes		X
Intrapartum fever		X
Small for gestational age (weight <10th centile for gestational age)		X
Infant gender		X
Meconium-stained liquor		X

BMI, body mass index; OASIS, Obstetric Anal Sphincter Injury.

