The main logistic model will incorporate these selected covariates through regression adjustment. Results will be reported as an unadjusted and adjusted ORs (comparing birth in water to on land), and a two-sided 90% CI for the unadjusted and adjusted OR will be calculated. Non-inferiority will be concluded if the upper limit of the 90% CI for the difference in infant outcome between the groups is less than 1.0% (OR <1.21). Similarly, for the mother’s outcome, non-inferiority will be concluded if the upper limit of the 90% CI for the difference in the proportion of OASIS between the groups is less than 1.0% (OR <1.23) in nulliparous low-risk women and less than 0.6% (OR <1.38) in parous low-risk women. The data will then be combined to assess the effects averaged across both strata.

If non-inferiority is shown, then superiority analysis will be conducted as secondary analysis of the primary outcomes using logistic regression and will be presented as (unadjusted and adjusted) OR of outcomes in the waterbirth group compared with the birth on land group. Parameter estimates will be provided alongside 95% CI and p value. Secondary outcomes will have non-inferiority testing as detailed above.

Secondary analysis will describe the type and rates of complications among (a) low risk women who left the pool due to clinical need along with the associated maternal and infant outcomes and (b) high risk women using a pool, along with associated care (for example use of waterproof CTG cardiotocography), and maternal and infant outcomes

Maternal characteristics such as age, parity and ethnicity of all women giving birth in the study sites during data collection will be obtained and the characteristics of women who do and who not use a pool during labour, will be compared and described.

All telephone and face-to-face discussions in phase 1 and phase 2 will be audiorecorded and transcribed verbatim. For phase 1 of the qualitative component, framework analysis will be undertaken to generate key hypotheses for further exploration in phase 2. In phase 2, data will be thematically analysed initially, supported by NVivo, in order to develop an analytic framework, which will then be used to code all data.

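### The stated 90% power belongs to an unadjusted risk-difference comparison; it is not shown for the adjusted logistic model named as the main analysis, and is lower if the odds ratio decides

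*Protocol article*

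**What the plan says.** The Sample size section takes OASIS rates from an earlier cohort in which "overall 4.6% and 1.6% of nulliparous and parous women respectively, sustained OASIS". It sets the target as "A sample size of 15 000 nulliparous and 15 000 parous low-risk women (7500 each water and land") and gives the maternal margins: "A non-inferiority margin of 1% or less, and 0.6% or less will be taken as clinically non-significant". For infants, "an estimate of 5% is used for the proportion of infants born to low-risk mothers" with an adverse outcome or treatment, with 8100 per group and this margin: "A non-inferiority margin of 1.0% or less will be taken as clinically non-significant". Each target carries the same claim, that the sample "is required to obtain 90% power, and a 95% one-sided CI around a treatment difference of zero". No covariate term or allowance for adjustment is mentioned.

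The Main analysis section runs an unadjusted logistic model first, then says "The main logistic model will incorporate these selected covariates through regression adjustment". It gives this ground for adjusting: "Adjusting for potential confounders may result in a more precise treatment effect estimate". The planned 90% intervals are for the unadjusted and adjusted odds ratios. The non-inferiority rule is worded as a limit on a difference, with odds ratios of 1.23 (nulliparous), 1.38 (parous) and 1.21 (infant) in brackets.

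**The concern.** The power figure and the main analysis describe two different tests. The first is a crude comparison of two proportions on the difference scale. The second is an adjusted logistic model reported as an odds ratio. Two things change between them: the scale of the margin and the variance of the estimate.

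Allocation is not random, as the article says under its limitations, so the adjusted result has to carry the safety conclusion. If its power is below the stated 90%, the risk of missing non-inferiority when waterbirth is in truth no worse is higher than readers are told. A missed margin could then be taken for a safety signal when the cause is lack of precision.

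**Working it through.** **Inputs.** From the Sample size section: event rates p of 4.6%, 1.6% and 5%; margins d of 1.0, 0.6 and 1.0 percentage points; 7500, 7500 and 8100 per group; one-sided 5%; true difference zero. From the Main analysis section: odds-ratio margins 1.23, 1.38 and 1.21. Not in the document: R², the share of variation in waterbirth explained by the selected covariates. It is assumed below, at 0.10 for the main illustration.

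**Step 1: reproduce the stated sizes.** For a crude risk difference, n per group = 2p(1−p)(1.645+1.282)²/d², where the squared term is 8.564 with unrounded quantiles.
- Nulliparous: 2 × 0.043884 × 8.564 / 0.01² ≈ 7516
- Parous: 2 × 0.015744 × 8.564 / 0.006² ≈ 7490
- Infant: 2 × 0.0475 × 8.564 / 0.01² ≈ 8136

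These match the stated 7500, 7500 and 8100. Power at the stated sizes is 89.9%, 90.0% and 89.9%, so nothing is held back for adjustment.

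**Step 2: check the bracketed odds ratios.** Odds of (p+d) over odds of p: 5.6% against 4.6% gives 1.230; 2.2% against 1.6% gives 1.383; 6% against 5% gives 1.213. The bracketed values are the crude equivalents of the difference margins.

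**Step 3: unadjusted power on the odds-ratio scale.** SE of the log odds ratio = √[2/(n p(1−p))]; power = Φ(ln(OR margin)/SE − 1.645).
- Nulliparous: SE 0.0780; 0.2070/0.0780 = 2.656; power 84.4%
- Parous: SE 0.1301; 0.3221/0.1301 = 2.475; power 79.7%
- Infant: SE 0.0721; 0.1906/0.0721 = 2.644; power 84.1%

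The loss arises because the log odds ratio at the margin is smaller than d/[p(1−p)], which is what the difference formula implies: 0.207 against 0.228, 0.322 against 0.381, and 0.191 against 0.211. No covariate is involved.

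**Step 4: add variance inflation.** Multiply the variance by 1/(1−R²), so that the ratio of margin to SE is multiplied by √(1−R²).

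| Comparison | Odds ratio, crude | Odds ratio, R² 0.10 | Difference, crude | Difference, R² 0.05 | Difference, R² 0.10 | Difference, R² 0.20 |
|---|---|---|---|---|---|---|
| Nulliparous | 84.4% | 80.9% | 89.9% | 88.6% | 87.0% | 83.4% |
| Parous | 79.7% | 75.9% | 90.0% | 88.7% | 87.1% | 83.5% |
| Infant | 84.1% | 80.6% | 89.9% | 88.5% | 87.0% | 83.3% |

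**Step 5: does adjustment improve precision?** A large-sample information calculation was run for a logistic model with group and one standard-normal covariate. The covariate's log odds ratio for the outcome was assumed at 0.3 to 1.0 per SD.
- Log odds ratio: the adjusted SE is 0.1% to 3% larger than the crude SE when the covariate is unrelated to group, and 1% to 13% larger at R² of about 0.02 to 0.12. It was never smaller.
- Standardised risk difference: the ratio of adjusted to crude SE runs from 0.97 to 1.10. Adjustment can narrow or widen this interval. At R² of about 0.02 to 0.12, power is about 86–91% (nulliparous), 84–90% (parous) and 86–91% (infant).

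**The case against.** A reader might infer that adjustment always widens the interval, so that 90% is a ceiling and the main test certainly falls short of it. The document does not support that, for four reasons.

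- **R² is not given.** Table 2 lists potential confounders, to be selected with causal diagrams, and both groups are low-risk pool users. R² may be small. At 0.05 the loss on the difference scale is about 1.4 points.
- **The rule is worded as a difference.** If a standardised risk difference decides, a prognostic covariate weakly related to waterbirth can hold power at 90% or slightly above. The remark on precision, which says only that a gain may occur, can be true there.
- **On the odds-ratio scale, adjustment is not the main cause.** The change of scale costs about 5 to 10 points; R² of 0.10 costs a further 3 to 4. An adjusted odds ratio is also conditional, so margins derived from crude rates are not exact for it. Using the matching conditional margin recovers part of the loss: for nulliparous women, from 82.6% to 86.5% with no confounding and a log odds ratio of 1.0 per SD.
- **More births may be analysed than required.** The article mentions six years of data and assumes 1650 nulliparous waterbirths a year: 6 × 1650 = 9900. With 9900 per group, power at R² of 0.10 would be 93.8% on the difference scale and 89.4% on the odds-ratio scale. The other three groups are expected to be larger.

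The first three points limit the claim and are accepted. The fourth shows that achieved power could be higher, but 1650 is not restricted to low-risk women, the infant outcome uses only births after site opening, and the 90% is claimed for 7500 and 8100 per group. Crude sizing followed by adjusted analysis is common, and the detail of an inflation factor may sit in the full protocol or analysis plan. What remains is that the article states one power figure and names a main model to which that figure has not been shown to apply.

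**Conclusion.** The concern holds in a limited form. The sample-size arithmetic is correct for what it computes: 90% is the power of an unadjusted risk-difference comparison. It is not shown for the adjusted main model.

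The shortfall depends on which scale decides. By the odds ratio against the bracketed margins, it is about 6, 10 and 6 points before adjustment and about 9, 14 and 9 points at an assumed R² of 0.10. By a standardised risk difference, it ranges from nothing to about 3 points at R² up to 0.10 under simple variance inflation. Both sets assume exactly the stated group sizes, the stated event rates and a true difference of zero.

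The precision rationale fails on the scale for which the intervals are planned, since adjustment does not improve the precision of the log odds ratio.

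**What to change.** 1. **Main analysis:** state whether the difference or the odds ratio decides non-inferiority. If the difference decides, say that it will be a standardised difference from the adjusted model.
2. **Sample size:** label 90% as the power of the crude risk-difference comparison. Add the power of the adjusted main model on the deciding scale. Take the variance inflation from a regression of waterbirth on the selected covariates that uses no outcome data, and use the group sizes actually available, separately for nulliparous women, parous women and infants.
3. **Main analysis:** replace the sentence on precision with control of confounding as the reason for adjustment.

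The cost is one outcome-free regression, a few sentences, and a stated power that will probably be less favourable than 90% at the required sizes. No new data collection is needed to make the statement correct.

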### Main analysis

Primary analysis will compare maternal and infant outcomes only between women without identified pregnancy or intrapartum complications ‘low risk’ who stay and give birth in the pool (waterbirth, group 1) compared with women without identified pregnancy or intrapartum complications ‘low risk’ who use water immersion during their labour but decide to leave the water for birth (out of water, group 2).

The primary analyses are based on a non-inferiority test of birth in water vs on land, comparing (1) the proportion of mothers that have OASIS (based on retrospective and prospective EuroKing data) and (2) the proportion of infants with a composite outcome of ‘adverse infant outcome or treatment’ (based on prospective EuroKing and NNRD data).

To test the primary hypothesis of non-inferiority between birth in water and on land, the maternal and infant primary outcomes will be evaluated for non-inferiority using logistic regression models, in the first instance with no adjustment for covariates. Adjusting for potential confounders may result in a more precise treatment effect estimate. The potential confounders of both primary outcomes (listed in table 2) will be considered. Directed acyclic graphs; visual representations of causal assumptions will be used to identify the presence of confounders.

**Table 2 T2:** Potential confounders for both maternal and infant primary outcomes

	**Maternal outcome: OASIS**	**Adverse infant composite outcome**
Maternal age (years)	X	X
Maternal BMI	X	X
Parity	X	
Duration of labour	X	X
Gestational age at delivery (weeks)	X	X
Birth weight (g)	X	X
Infant head circumference (cms)	X	
Maternal thyroid disease (including hypothyroidism)		X
Prelabour ruptured membranes		X
Intrapartum fever		X
Small for gestational age (weight <10th centile for gestational age)		X
Infant gender		X
Meconium-stained liquor		X

BMI, body mass index; OASIS, Obstetric Anal Sphincter Injury.

The main logistic model will incorporate these selected covariates through regression adjustment. Results will be reported as an unadjusted and adjusted ORs (comparing birth in water to on land), and a two-sided 90% CI for the unadjusted and adjusted OR will be calculated. Non-inferiority will be concluded if the upper limit of the 90% CI for the difference in infant outcome between the groups is less than 1.0% (OR <1.21). Similarly, for the mother’s outcome, non-inferiority will be concluded if the upper limit of the 90% CI for the difference in the proportion of OASIS between the groups is less than 1.0% (OR <1.23) in nulliparous low-risk women and less than 0.6% (OR <1.38) in parous low-risk women. The data will then be combined to assess the effects averaged across both strata.

If non-inferiority is shown, then superiority analysis will be conducted as secondary analysis of the primary outcomes using logistic regression and will be presented as (unadjusted and adjusted) OR of outcomes in the waterbirth group compared with the birth on land group. Parameter estimates will be provided alongside 95% CI and p value. Secondary outcomes will have non-inferiority testing as detailed above.

Secondary analysis will describe the type and rates of complications among (a) low risk women who left the pool due to clinical need along with the associated maternal and infant outcomes and (b) high risk women using a pool, along with associated care (for example use of waterproof CTG cardiotocography), and maternal and infant outcomes

Maternal characteristics such as age, parity and ethnicity of all women giving birth in the study sites during data collection will be obtained and the characteristics of women who do and who not use a pool during labour, will be compared and described.

All telephone and face-to-face discussions in phase 1 and phase 2 will be audiorecorded and transcribed verbatim. For phase 1 of the qualitative component, framework analysis will be undertaken to generate key hypotheses for further exploration in phase 2. In phase 2, data will be thematically analysed initially, supported by NVivo, in order to develop an analytic framework, which will then be used to code all data.

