This study is collecting data on births to all women in 26 UK maternity units from 2015 and is identifying the numbers, proportion and characteristics of women who use water immersion during labour or birth. The study will also establish whether waterbirth is as safe for mothers and their infants as using a pool during labour but getting out prior to birth. Data will be collected on 15 000 waterbirths and 15 000 land births among women with uncomplicated pregnancies from National Health Service (NHS) sites which use Wellbeing Software’s (WS) maternity software system EuroKing. This study will use data recorded routinely as part of standard maternity care and stored on respective NHS site’s servers. For infants admitted to a neonatal unit (NNU), the study will also use data held by the National Neonatal Research Database (NNRD). Data needed to answer some study questions are already recorded, for example, perineal trauma, therefore, data from births from 2015 onwards can be included. Existing, routinely collected data does not capture all information to answer the study questions, data items missing from existing routinely collected data include infants receiving antibiotics without admission to NNU and whether following waterbirth the placenta is delivered in or out of water. Cardiff University (CU) has worked with WS in order to develop study specific data fields which will enable these data to be captured in participating sites from 2019 onwards.

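### The primary models as described and the sample size make no allowance for maternity unit, so the 5% error holds only if units are alike in the relevant respects

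*Protocol article*

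**What the plan says.** Under Main analysis, the two primary outcomes are to be "evaluated for non-inferiority using logistic regression models, in the first instance with no adjustment for covariates". For the adjusted analysis, "The main logistic model will incorporate these selected covariates through regression adjustment", with candidates taken from Table 2. That table lists maternal, labour and infant characteristics. It contains no maternity unit, unit type or region. Non-inferiority is judged by the upper limit of a two-sided 90% CI.

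Under Sample size, the article uses the finding that "overall 4.6% and 1.6% of nulliparous and parous women respectively, sustained OASIS", and states that "A non-inferiority margin of 1% or less, and 0.6% or less will be taken as clinically non-significant" for nulliparous and parous women respectively. The number in each parity stratum "is required to obtain 90% power, and a 95% one-sided CI around a treatment difference of zero". The infant calculation uses a 5% event rate, a 1.0% margin and 8100 per group. No intracluster correlation or design effect is given.

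On the source of the data, the Introduction says: "This study is collecting data on births to all women in 26 UK maternity units from 2015". Factors associated with pool-use rates in individual units are a secondary objective. The case-study sites for the qualitative work are to be identified from site data, "enabling the team to work with sites with both low and high waterbirth rates".

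**The concern.** Births in one maternity unit share staff, practice, recording habits and thresholds for treatment. Rates of recorded OASIS and of infant antibiotic use may therefore differ between units, and so may the share of pool users who stay in the water for the birth. When both differ, the crude water/land comparison partly compares high-rate units with low-rate units. A standard error that treats every birth as independent misses this source of variation.

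The direction matters. Non-inferiority rests on the upper confidence limit, so an interval that is too narrow favours declaring waterbirth safe when it is in fact at the margin.

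**Working it through.** **Reproducing the stated sizes.** The inputs are one-sided 5%, 90% power, true difference zero, and the rates and margins in the Sample size section. With independent births, n per group = 2p(1−p)(1.645 + 1.282)²/d², where the squared term is 8.564.

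- Nulliparous: 2 × 0.046 × 0.954 × 8.564 / 0.01² = 7517 (stated 7500)
- Parous: 2 × 0.016 × 0.984 × 8.564 / 0.006² = 7491 (stated 7500)
- Infant: 2 × 0.05 × 0.95 × 8.564 / 0.01² = 8136 (stated 8100)

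The stated sizes are the independent-births sizes and leave no room for a design effect.

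**Design effect for an exposure that varies within units.** DE = 1 + (m − 1) × ρx × ρy. Here m is births per unit, ρx = SD²/0.25 describes between-unit variation in the water share (around one half), and ρy = (CV × p)²/[p(1−p)] describes variation in the outcome rate. The article gives neither ρ. The assumed range is a split SD of 10 to 20 points (ρx = 0.04 to 0.16) and an outcome CV of 20 to 30%. Average unit size is 15 000/26 = 577 per parity stratum and 16 200/26 = 623 for infants. True one-sided error with the independent-births interval is 1 − Φ(1.645/√DE).

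| Outcome | m | ρy (CV 20%, 30%) | DE (low, high) | Error (low, high) |
|---|---|---|---|---|
| Nulliparous OASIS | 577 | 0.00193, 0.00434 | 1.044, 1.400 | 5.4%, 8.2% |
| Parous OASIS | 577 | 0.00065, 0.00146 | 1.015, 1.135 | 5.1%, 6.1% |
| Infant composite | 623 | 0.00211, 0.00474 | 1.052, 1.471 | 5.4%, 8.8% |

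Example, infant, high end: 1 + 622 × 0.16 × 0.00474 = 1.471; √1.471 = 1.213; 1.645/1.213 = 1.356; upper tail 8.8%.

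**Simulation for nulliparous OASIS, 26 units, true difference at the margin.**

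- Same split in every unit and a common effect: error 4.6 to 5.0%, power about 90%, even when outcome rates differ between units.
- High end of the assumed range (split SD 20 points, CV 30%): error 7.6 to 7.8%.
- Analysis stratified by unit, common effect: error returns to about 5%. Over the assumed range power is about 85 to 89%, or 83 to 88% with cluster-robust variance.

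**Effect that varies between units.** Take an SD of 1 point, equal splits and no other variation. The independent-births SE at the margin is √[(0.046 × 0.954 + 0.056 × 0.944)/7500] = 0.00359. Adding 0.01²/26 to its square gives 0.00409, a ratio of 1.139. The error is then 1 − Φ(1.645/1.139) = 7.4%. Simulations gave 7.6 to 8.0%. Stratifying by unit left it at 7.5%. With the 26 unit effects held fixed rather than redrawn, it was 5.1%.

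**The case against.** The strongest reply is that a condensed article's silence on unit is weak evidence. A logistic model with a random intercept or robust variance is still logistic regression, and an analysis plan that is not shown may specify one. That stands for the model. It does not cover the Sample size section, which is in the article and reproduces under independence.

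A reader might go further and infer that the intervals certainly are too narrow, and that the 5% error and 90% power are not delivered. The documents do not support this. Exposure varies between women within each unit, so the design effect for whole-cluster allocation, 1 + (m − 1) × ICC, does not apply. The article quantifies neither the between-unit split nor the outcome variation. The remark about low and high waterbirth rates concerns the choice of case-study sites. A unit's waterbirth rate also depends on pool access and case mix, so it is not the split among low-risk pool users who left without a clinical reason.

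Three further points stand:

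- Where split and rate both vary, much of the problem is imbalance between units, and a unit term removes it. Applying the infant design effect of 1.471 to power gives Φ(2.926/1.213 − 1.645) = 78%. That overstates the loss once unit is in the model, and no large increase in sample size follows.
- The heterogeneity result treats the 26 units as a sample from a wider population. For the average effect in these units alone, the error stays near 5%. An SD of 1 point is also as large as the whole nulliparous margin.
- Repeat births to one woman are a possible further dependence, but nothing in the article allows a magnitude.

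**Conclusion.** The point holds conditionally. As described, neither the primary models nor the sample size allow for maternity unit, in a study of 26 units where unit differences in pool use are themselves an object of study.

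The consequence depends on assumptions the article does not settle. The error exceeds 5% only if units differ in both split and outcome rate, or if the effect varies and inference is meant to extend beyond these units. At the mild end of the assumed range the excess is negligible. At the strong end the error is 8 to 9% for nulliparous OASIS and the infant composite by formula. The parous figures apply at the planned size. A larger parous sample would raise power, but also births per unit and so the design effect.

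**What to change.** In Main analysis, state that both the unadjusted and the adjusted primary CIs account for maternity unit: a unit term (fixed or random intercept) with cluster-robust variance corrected for the small number of clusters, 26. Add a model with a random waterbirth effect by unit as a sensitivity analysis, and say whether inference is to these units or beyond them.

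In Sample size, state that 90% power assumes independent births. Give a range of power under plausible between-unit variation, about 83 to 89% for nulliparous OASIS with unit adjustment and a common effect. Retrospective data can inform the OASIS range. The infant composite needs early prospective data, because its items are collected only from site opening. Some items that help to define the two groups, such as risk status at pool entry and reasons for leaving, also start then, so a retrospective OASIS estimate will be approximate.

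The cost is a change of wording, slightly wider intervals, and a stated power somewhat below 90%. No new data are needed.
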